## **6.5 Symptom scales**

### **6.5.1 Daily diary about stool frequency and consistency**

The participants will complete a daily diary about their stool frequency and consistency based on the Bristol Stool Chart (Appendix V).

### **6.5.2 IBS - severity scoring system (IBS-SSS)**

This scale developed by Francis et al. is an additional tool to assess IBS symptoms. It evaluates five aspects of IBS during a 10-day period: abdominal pain, distension, stool frequency and consistency and interference with daily life (Appendix VI). Each item is scored on a visual analogue scale from 0 to 100 and the sum is the total score. The scale is responsive to treatment and has good validity, and takes about 5 min to complete (Drossman et al. 2011).

### **6.5.3 Gastrointestinal Symptom Rating Scale - IBS (GSRS-IBS)**

The GSRS-IBS a reliable, valid IBS-specific symptom scale (Wiklund et al. 2003). It includes 13 items in five symptom clusters: abdominal pain, bloating, constipation, diarrhea and satiety (Appendix VII). It measures symptoms during the past 7 days with a 7-point Likert scale ranging from 1 (no discomfort at all) to 7 (very severe discomfort), and takes about 5 min to complete.

### **6.5.4 Quality of life scale for IBS patients (IBS-QOL)**

This 26-item questionnaire developed by Wong et al. includes the following areas: bowel symptoms, fatigue, activity limitations and emotional dysfunction (Wong et al. 1998) (Appendix VIII).

### **6.5.5 Health-related quality of life (EuroQol EQ-5D-5L)**

This is a standardized measure of health status developed by the EuroQol Group in order to provide a simple, generic measure of health for clinical and economic use (The EuroQol 1990) (Brooks 1996) (Janssen et al. 2012). The questionnaire is applicable to a wide range of health conditions and treatments. It consists of 5 items related to wellbeing and function and provides a simple descriptive profile and a single index value for health status (Appendix IX). In addition, the instrument consists of a scale where the study subject can rate her or his own experienced health status.

### **6.5.6 Hospital anxiety and depression scale (HADS)**

This scale was originally developed by Snaith and Zigmond for use in a medical setting, and its validity and reliability has been reported in several studies (Snaith and Zigmond 1986). It consists of 14 items divided into two subscales for anxiety (seven items) and depression (seven items) (Appendix X). Patients rate each item on a four-point scale. A cut-off of  $> 11$  implies definite cases of anxiety or depression, a cut-off of 8–10 a probable case, and  $\leq 7$  no case. It takes about 5 min to complete the questionnaire.

### **6.5.7 Perceived stress scale (PSS)**

This scale is the most widely used psychological instrument for measuring the perception of stress (Appendix XI). It is a measure of the degree to which situations in one's life are appraised as stressful. Items were designed to tap how unpredictable, uncontrollable and overloaded the respondents find their lives. The scale also includes a number of items about current levels of experienced stress. PSS demonstrate high reliability (i.e., Cronbachs alpha = 0.84-0.86; test-retest reliability  $r = 0.85$ ) and the scale correlates adequately with for example other stress measures, self-reported health and health behavior measures (Cohen, Kamarck, and Mermelstein 1983). This scale takes approximately 5 minutes to fill out.

### **6.6 Permeability assay**

At visit 2-5, the intestinal permeability will be measured using a standardised multi-sugar test, which is a sensitive, non-invasive technique able to detect small changes in small and large intestinal permeability. For this procedure, 150 ml of tap water containing 1 g sucrose, lactulose, sucralose, erythritol and 0.5 g rhamnose will be orally administered after an overnight fast, followed by total urinary collection for 24 hours. During the first five hours of urine collection, the participants will refrain from food intake, and will be asked to drink at least 1.5 litres of provided water. Urine will be collected by the subjects in the provided urine bottles (3L, brown with yellow lid) and stored in cooling bags. After finalizing the five hours urine collection, subjects will continue to collect their urine for 19 hours in the provided urine bottles stored in the provided cooling bags. The study participants will return the urine samples to the university staff the following day. See chapter 8 for dietary restrictions for the participants before and during sample collection.

The urine samples will be centrifuged, aliquoted and stored at  $-80^{\circ}\text{C}$  until further analysis by High Performance Liquid Chromatography (HPLC) to detect urinary excretion ratios of the sugars.

### **6.7 Collection of blood**

Blood will be collected from each subject at visit 2-5 for analysis of the markers related to intestinal permeability and/or inflammation such as intestinal fatty acid binding protein (i-FABP), zonulin, bacterial 16S ribosomal RNA (16S rRNA) gene copy number, vasoactive intestinal polypeptide (VIP), and cytokines. Plasma, serum and whole blood will be aliquoted into cryogenic vials and frozen.

### **6.8 Cortisol awakening rhythm (saliva)**

For the cortisol awakening rhythm, subjects will be instructed to collect saliva samples at home for three consecutive days before visits 2-5. Participants will collect the samples using a salivette directly after awakening as well as 15, 30, 45, and 60 minutes thereafter. Subjects are free to use an alarm clock or to wake up spontaneously. Subjects will be instructed not to brush their teeth before completing saliva sampling to avoid contamination of saliva with blood caused by micro-injuries in the oral cavity. Subjects will be asked to refrain from food intake and beverages containing alcohol, caffeine or fruit juices as well as smoking during the

sampling period. Besides these restrictions, subjects will be free to follow their normal morning routines on the sampling day.

## **6.9 Collection of faecal samples**

For analysis of the faecal microbiota composition, faecal samples will be collected at visit 2-5. Subjects will collect faecal samples at home using provided faecal samples tubes (using a spoon inside the tube). The samples will be aliquoted into four vials and immediately placed into the home freezer by the subjects, and will be returned frozen to the study unit using special cool transport containers. At the study unit the faecal samples will be stored at -80°C. Faecal samples will be analysed for inflammation and barrier function markers such as faecal calprotectin and zonulin. In addition, faecal samples will be used for microbiota composition analysis (16S rRNA-based next generation sequencing, NGS) and metabolomics (microbial metabolites profile).

## **7 Concomitant treatment**

Participants will be instructed not to take NSAIDs (e.g. ibuprofen, aspirin), anticholinergic drugs, steroids, antibiotics or antimicrobial medication, oral mast cell stabilising drugs e.g. sodium cromoglycate, and pre- and probiotic products during the study.

Any other medication, if considered necessary for the patient (e.g. (laxatives, antidiarrheals), with a stable dose (when possible) can be used but should be restricted to a minimal dose. Any treatment ongoing before the study and changes in its doses will be recorded in the CRF. In addition, subjects will record any treatment prescribed during the study.

## **8 Restrictions and instructions for study participants**

The subjects will be asked to avoid changes in their diet and life style, such as training and sleep habits, during the study. Intake of probiotic products, as well as food and food supplements containing probiotics are not allowed from 4 weeks before the screening visit until the end of the study. Subjects will not be withdrawn from the study due to single violations, but violations will be recorded as protocol deviations. Any use of illicit drugs (euphorics or stimulants, such as cannabis, opium) is prohibited during the study. Subjects will be carefully instructed to:

- Refrain from taking any NSAIDs, antibiotics, anticholinergic drugs, oral mast cell stabilising drugs, and pre- and probiotics during the study period.
- Refrain from consuming alcohol two days prior each visit and during the 24h urine collection.
- Refrain from consuming nicotine two days prior each visit and during the 24h urine collection.
- Refrain from consuming spicy food two days prior to each visit and during the 24h urine collection.
- Refrain from consuming the artificial sugars sucralose, erythritol, lactulose and rhamnose (contained in the sugar mix) two days prior to each visit and during the 24h urine collection.
- Avoid strenuous exercise two days prior to each visit and during the 24h urine collection.

- Have the same meal in the evening prior to each visit.
- Refrain from consuming caffeine the day of each visit and during the 24h urine collection.
- The subjects shall drink at least 1.5 litres of provided water and fast (no food intake) during the first 5 hours of urine collection.

## **9 Safety and ethical considerations**

The probiotic compounds will be studied in volunteer IBS patients, and participants will be informed about potential risks and that participation in the study may be discontinued at any time. Probiotics are known to have health-beneficial effects on gut functioning, however, mechanisms behind possible benefits from probiotics remains uncertain and thus more mechanistic studies can be justified.

Collection of faecal samples, urine and saliva is not painful or risky for the patients but it could be bothersome for some of the participants. Collection of blood will be performed by experienced nurses according to hospital routines and could in some cases cause discomfort, pain, swelling and bruising.

Participation in the study is voluntary and all subjects have the right to withdraw from the study at any time without affecting their normal treatment. Prior to any study-related activity, the study staff will give the subject oral and written information about the study. A voluntary, signed and dated informed consent form will be obtained from the patients prior to any study-related activity. This study will be conducted according to good clinical practice and the ethics of the Helsinki declaration.

Written approval will be obtained from the Central Ethical Review Board of Uppsala prior to commencement of the study.

## **10 Withdrawal criteria**

The subject may withdraw at any time. The subject may be withdrawn from the trial by investigator or sponsor due to clinical or other reasons, if necessary. The subjects who meet any of the following criteria must be withdrawn from the study at the time of confirmation:

1. Non-IBS gastrointestinal disease in need for medical care.
2. Subject undergoing gastrointestinal surgery during the study.
3. Pregnancy.

In case of withdrawal, the withdrawal form in the CRF must be completed. Randomized subjects who do not complete the trial will be replaced (proof-of-concept study using a per-protocol analysis).

## **11 Adverse events**

Any adverse events and adverse effects will be recorded on the CRF by the investigators. The diagnosis, if available, or each sign or symptom should be recorded. All adverse events observed must be recorded separately. Onset day and resolution day will be recorded for each event.

The investigator will assess each event with regard to its severity:

- Mild: Transient symptoms, no interference with the subject's daily activities.
- Moderate: Marked symptoms, moderate interference with the subject's daily activities but still acceptable.
- Severe: Considerable interference with the subjects daily activities, unacceptable.

The investigator will assess the causality of the FMT for each adverse event in the following manner:

- Unrelated: FMT has not been performed yet.
- Unlikely: The event is most likely related to an aetiology other than the FMT.
- Possible: A causal relationship is conceivable and cannot be dismissed.
- Probable: Good reason and sufficient documentation to assume a causal relationship.

Any pharmacological treatments used for the event will be recorded.

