#### 4 Study design

This will be a single-centre, randomised, double-blinded, placebo-controlled intervention study with a parallel design and three study arms.

The study will investigate the effects of supplementation with the probiotic products *L. reuteri* ATCC PTA 6475 and Gastrus (*L. reuteri* DSM 17938/ATCC PTA 6475) on the intestinal barrier function, gut health and stress symptoms in diarrhoea-predominant IBS (IBS-D) patients. The test product is a tablet containing either ATCC PTA 6475 or Gastrus (DSM 17938/ATCC PTA 6475). The subjects will consume the product twice a day, giving a daily dose of  $1 \times 10^9$  CFU of each strain. The placebo product is an identical tablet except for the absence of probiotics. After having given their written informed consent, subjects will complete screening procedures to evaluate their eligibility for the study (visit 1). Study participants will undergo two baseline visits (visits 2 and 3, 3 weeks apart) to account for individual variations, and will then be randomly assigned to 6-week intake of either ATCC PTA 6475, Gastrus, or placebo in a ratio of 1:1:1 (stratified by sex). Participants will attend a study visit three weeks into the intervention (visit 4) and at the end of the intervention (visit 5, week 6). The intestinal permeability will be assessed using a standardized multi-sugar test at visit 2, visit 3, visit 4, and at end of intervention (visit 5). Blood, saliva and faecal samples will be collected at visit 2-5. In addition, gastrointestinal symptoms will be recorded at those visits (using GSRS-IBS, IBS-SSS). Quality of life using the 5Q-5D-5L and Hospital Anxiety and Depression Scale (HADS) scores will also be recorded at those visits. In addition, at visit 3 and visit 5, the IBS-QoL and the Perceived Stress Scale (PSS) will be completed. In a daily diary, participants will record stool frequency and consistency from visit 2 until end-of-study visit 5. Dietary habits of the patients will be assessed via a food frequency questionnaire (FFQ) and a 3-day food diary before the intervention (between visit 2 and 3).

During the entire run-in and intervention period, the subjects will be asked not to consume any probiotic products other than the study products. During the entire study subjects should maintain their habitual diet and life style such as physical activity level and sleep habits.

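### The only adverse-event causality scale (Section 11) refers to FMT, which no arm receives, so relatedness to the study tablets is never recorded as written

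*Protocol*

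**What the plan says.** Section 11 has the investigator record each adverse event separately, with the diagnosis or the sign or symptom, the onset and resolution days, a three-level severity grade and any drug treatment given. It then sets the causality assessment: "The investigator will assess the causality of the FMT for each adverse event in the following manner". Four categories are given. The lowest is defined by timing alone: "Unrelated: FMT has not been performed yet". The next one up is defined by a competing cause: "Unlikely: The event is most likely related to an aetiology other than the FMT". Above these stand Possible, for a link that can be imagined and not ruled out, and Probable, for a link with well-documented grounds.

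The first two name FMT. The last two name no exposure and take it from the sentence that introduces the list.

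Section 4 describes the interventions differently. On the active products it states: "The test product is a tablet containing either ATCC PTA 6475 or Gastrus". On the control it states: "The placebo product is an identical tablet except for the absence of probiotics". Section 6.3 specifies tablets taken twice daily. Sections 3 and 9 likewise speak only of probiotic products.

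**The concern.** A causality scale has to name the exposure whose effect is being judged. This one names an intervention that is not part of the trial, and the protocol has no other causality scale to fall back on. Investigators must then either apply the definitions as printed, which gives no information about the tablets, or improvise by reading FMT as the study product. If they differ in which they do, the field will be inconsistent.

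This cannot be left to the analysis plan. Causality is judged by the investigator, event by event, while the trial runs, and an analysis plan can only tabulate what was collected. At stake is whether the trial can say which events were thought related to either probiotic product or to placebo.

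**Working it through.** No figure is involved, so the check sets the sections side by side and applies each definition in turn.

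**Step 1: is FMT given to anyone?** The objectives (Section 3), the design and flow chart (Section 4, Table 1), the product description (Section 6.3), randomisation (Section 6.4) and the safety section (Section 9) describe three arms: two *L. reuteri* tablet products and placebo. No arm, visit or flow-chart row contains FMT. In the text available, the abbreviation occurs only in Section 11 and is not expanded.

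**Step 2: apply each category literally to a participant who never receives FMT.**

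| Category | Condition | Result for any event |
|---|---|---|
| Unrelated | FMT not yet done | Always true |
| Unlikely | Cause is most likely something other than FMT | Always true |
| Possible | FMT is a conceivable cause | Cannot apply |
| Probable | Good grounds to attribute the event to FMT | Cannot apply |

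Two categories fit every event at once and two fit none. The scale therefore separates no event from any other, and none of its categories refers to the tablets.

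**Step 3: would replacing the word be enough?** With the study product in place of FMT, Unlikely, Possible and Probable become usable. Unrelated would mean that the product had not yet been started. The product is taken twice daily for six weeks, so after the first tablet no event could be classed as Unrelated, however plain its other cause. The flow chart appears to mark adverse-event reporting only in the intervention period (the table layout may be imperfect). If so, Unrelated would be almost or entirely empty.

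**Step 4: what is unaffected?** Event recording, dates, severity grades and concomitant treatment in Section 11 do not depend on FMT, nor do the withdrawal criteria in Section 10. No endpoint in Section 3 and no analysis in Section 12 uses relatedness.

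**The case against.** The strongest reply is that this is a slip that any investigator would read through, taking FMT to mean the study product, and that nothing planned in the trial depends on it. Much of that stands. Section 3 lists no safety or tolerability endpoint, and Section 12 plans no analysis of relatedness. In a randomised, double-blind, placebo-controlled trial, all-cause events by arm, with severity and timing, support a comparison that needs no attribution by the investigator.

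It can also be said that reserving Unrelated for events before exposure is a conservative convention, since Unlikely covers events with another probable cause. That is arguable for a single procedure. For a tablet taken daily over six weeks, it leaves no way to record that an event plainly had another cause.

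The reply does not remove the error. The protocol nowhere says that FMT stands for the study product, and an operative instruction should not depend on a guess.

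Several stronger inferences are tempting, and the protocol does not support them:

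- **That this is the protocol's only safety rule.** It is the only causality rule; Sections 10 and 11 contain others.
- **That no statement on tolerability against placebo would be possible.** All-cause comparisons by arm remain.
- **That every event will be recorded as Unrelated, giving zero related events among the 75 planned participants.** The literal reading satisfies Unlikely equally well, and it does not predict what investigators will enter. The 75 is not a ceiling either, since Section 10 replaces randomised non-completers.
- **That the CRF carries the same error.** No adverse-event CRF page is available to check.
- **That the text was carried over from a faecal transplantation trial.** This is plausible but undocumented, and the point does not need it.

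**Conclusion.** The causality scale is wrong as written, and the fault is limited to the relatedness field. Taken literally, it applies to every adverse event in all three arms and yields no information on relatedness to the study products. All-cause event counts by arm, severity, dates, the primary efficacy analysis and the sample size are unaffected.

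The conclusion rests on two things: the protocol text available contains no other causality scale, and it nowhere defines FMT as the study product. How far the recorded data would suffer depends on how investigators read the instruction and on what the CRF field says, and neither can be determined from the protocol.

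**What to change.** Three changes:

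1. Replace FMT throughout Section 11 with the (blinded) study product.
2. Redefine Unrelated as onset before the first tablet, or an event clearly explained by another cause. This makes the category usable once dosing has started. It also keeps it distinct from Unlikely, where another cause is the more probable one but is not clear.
3. Check that the causality field in the CRF uses the same wording, and align it if it does not.

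The cost is protocol wording and, if needed, CRF wording. No visit, procedure, endpoint or sample-size change follows.

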## **12 Data management and statistical analysis**

The investigators will ensure that the subject's anonymity will be maintained. On all documents, subjects will be identified only by a subject number – not by their names or personal number.

All statistical tests will be assessed using a nominal two-sided significance level of 5%.

The primary efficacy analysis will be based on difference in lactulose/rhamnose ratio before and after intervention for the two probiotic strains as compared to placebo. The difference between before and after intervention observed in either of the two probiotic strains will be compared to that difference observed for the placebo arm of the study using the two-sided Mann-Whitney U-test for independent samples (as in Zuhl et al. 2014 and similar studies).

Biomarker levels studied in plasma, serum and stool samples will be evaluated on log-scale, where appropriate, using the appropriate non-parametric univariate tests (e.g. Wilcoxon signed-rank test, Mann-Whitney U-test), as well as multivariate analyses using appropriate cross-validation approaches (as detailed in the SAP). Questionnaires will be evaluated using both logistic regression analyses of responder proportions as well as ANOVA for original response values. Microbiota phylogenetic profiles (NGS results) will be assessed by both uni- and multivariate analyses on the species- and genus-like phylogenetic levels, as well as on in-depth functional levels based on whole genome shotgun sequencing (NGS results).

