## 3 Study objectives

**The overarching aim** of this study is to investigate the effect of a 6-week intervention with two different probiotic products ((*Lactobacillus reuteri* ATCC PTA 6475 och Gastrus (*Lactobacillus reuteri* DSM 17938/ATCC PTA 6475)) on the intestinal permeability of diarrhoea-predominant IBS (IBS-D) patients.

**The primary endpoint** is the difference in small intestinal permeability, measured as the urinary lactulose/rhamnose secretion ratio, after a 6-week intervention with the probiotic products compared to the placebo product, in IBS-D patients.

**Secondary endpoints** are the differences between intervention with the probiotic products compared to the placebo in IBS-D patients on:

- The small intestinal permeability, measured as the urinary lactulose/rhamnose secretion ratio, after 3-week intervention
- Whole gut permeability measured as urinary sucralose/erythritol excretion ratio (0-24hrs) after 3 and 6 weeks
- Colonic permeability measured as urinary sucralose/erythritol ratio (5-24hrs) after 3 and 6 weeks
- Gastroduodenal permeability measured as urinary sucrose excretion (0-5hrs) after 3 and 6 weeks
- Various potential biomarkers of general intestinal barrier function and inflammation in blood and faecal samples after 3 and 6 weeks such as plasma i-FABP, faecal zonulin, serum zonulin, bacterial 16S ribosomal RNA (16S rRNA) gene copy number (whole blood), plasma vasoactive intestinal polypeptide (VIP), plasma high-sensitive C-reactive protein (hs-CRP), faecal calprotectin and plasma cytokines (e.g. IL-6 and IL-10)

**Exploratory endpoints** are the effects of the intervention with the probiotic products in comparison to the placebo in IBS-D patients on:

- Stool frequency and consistency (Daily diary on bowel movement using Bristol Stool Chart)
- Gastrointestinal symptoms as measured by the GSRS-IBS and IBS-SSS after 3 and 6 weeks
- Quality of life after 3 and 6 weeks (5Q-5D-5L, IBS-QOL)
- Perceived stress after 6 weeks (using the Perceived stress scale, PSS)
- Anxiety and depression symptoms after 3 and 6 weeks (HADS)
- Cortisol awakening rhythm (saliva) after 3 and 6 weeks
- Intestinal microbiota composition (16S rRNA-based next generation sequencing of faecal samples) after 3 and 6 weeks
- Metabolomic profile of faecal samples and blood, including SCFA metabolism and tryptophan catabolites such as 5-HT and melatonin, after 3 and 6 weeks.

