## 5 Study population

### 5.1 Number of subjects

The sample size is based on the ability to find a significant lactulose/rhamnose ratio difference between one of the probiotic study arms and the placebo arm. A relevant change of 15% in lactulose/rhamnose difference should be detected as significant, which according to the study by Zuhl et al. 2014 amounts to 0.009 points in ratio difference.

The sample size calculation is based on the following assumptions:

- 80% power
- An expected SD of 0.01 (Zuhl et al. 2014)
- Significance (alpha) level of 5%
- Two-sided testing (significance level of 5%)

To account for a potential drop-out rate of 15%, a total of 75 subjects will be randomized (N=25 subjects in each group should be included).

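### Section 12 applies a nominal 5% level to every test while planning univariate microbiota analyses, so as written individual taxa would be called significant without false discovery rate control

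*Protocol*

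**What the plan says.** Section 12 sets one level for everything: "All statistical tests will be assessed using a nominal two-sided significance level of 5" per cent. No exception, hierarchy or adjustment appears elsewhere in the protocol.

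The same section then says: "Microbiota phylogenetic profiles (NGS results) will be assessed by both uni- and multivariate analyses on the species- and genus-like phylogenetic levels". That sentence goes on to functional levels from shotgun sequencing. Section 3 lists microbiota composition, after 3 and 6 weeks, as an exploratory endpoint. The metabolomic profile is also exploratory, and Section 12 names no test for it.

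The secondary endpoints in Section 3 are four permeability measures and a biomarker list that begins "Various potential biomarkers of general intestinal barrier function and inflammation in blood and faecal samples after 3 and 6 weeks such as" and names nine markers. Section 4 randomises to three arms "in a ratio of 1:1:1 (stratified by sex"), so each endpoint has two product-versus-placebo contrasts.

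Section 12 refers to the SAP once, at the end of the sentence on biomarker analyses. The sentences on the 5% level and on the microbiota carry no such reference.

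**The concern.** A 5% level per test is reasonable for a few pre-named comparisons. It works badly when the same question is put to a long list of taxa or functional features. The number of chance findings then grows with the length of the list, whether or not the products do anything, and a reader cannot tell what share of the reported features is real.

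At stake is the credibility of the microbiota results. Section 9 justifies the trial partly by the need for more mechanistic work. If the sentence is followed literally, product effects on named taxa could be reported with an uncontrolled false share.

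**Working it through.** **The plan's own figure.** The protocol gives neither a count of tests nor an expected number of false positives. Its one computed figure, the sample size in Section 5.1, shows what the 5% level was set for. The inputs are a difference that "amounts to 0.009 points in ratio difference", "An expected SD of 0.01", 80% power, 15% drop-out and "Two-sided testing (significance level of 5" per cent).

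- Normal approximation: 2 × (1.960 + 0.842)² × (0.01/0.009)² = 2 × 7.851 × 1.2346 = 19.4, so 20 per arm; 20/0.85 = 23.5, so 24.
- t-test version: 20.4, so 21 per arm; 21/0.85 = 24.7, so 25.

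The stated 25 per arm is reproduced. It rests on one probiotic-versus-placebo contrast on one endpoint, and feature-level testing plays no part in it.

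**Feature-by-feature tests at an unadjusted 5%.** The expected number of false hits, if neither product has any effect, is features × contrasts × timepoints × 0.05. The two contrasts come from the three-arm design and the two timepoints from Section 3. The number of features is not in the protocol and is assumed here, counted over all taxonomic levels tested.

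| Features (assumed) | Contrasts | Timepoints | Tests | Expected false hits |
|---|---|---|---|---|
| 50 | 2 | 1 | 100 | 5 |
| 50 | 2 | 2 | 200 | 10 |
| 100 | 2 | 2 | 400 | 20 |
| 300 | 2 | 2 | 1200 | 60 |

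These expectations do not depend on correlation between tests. They do assume that each test has a true size of 5%. Functional features and metabolites are not counted.

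**Secondary tests that can be counted from Section 3.**

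- Lactulose/rhamnose ratio at 3 weeks: 1.
- Sucralose/erythritol 0–24 h, sucralose/erythritol 5–24 h and sucrose excretion, at two timepoints each: 2 + 2 + 2 = 6.
- Nine named biomarkers (plasma i-FABP, faecal zonulin, serum zonulin, 16S rRNA gene copies, VIP, hs-CRP, calprotectin, IL-6, IL-10) at two timepoints: 18.
- Total: 1 + 6 + 18 = 25, times two contrasts = 50 tests.
- Expected false positives: 50 × 0.05 = 2.5.
- Chance of at least one: 1 − 0.95^50 = 92.3% if the tests were independent. In simulation it is about 80% with a common correlation of 0.3 and about 62% with 0.5.

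**What false discovery rate control changes.** If a product affects no feature in a family, Benjamini-Hochberg at 5% keeps the chance of any false call in that family at or below 5%, for independent or positively dependent tests. As an example, take 100 features in one data block, with both timepoints in one family per contrast. That is 200 tests per family. At an unadjusted 5%, each such family would give 200 × 0.05 = 10 false hits in expectation.

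**The case against.** The strongest objection is that handling of multiplicity for exploratory sequencing data is commonly left to the SAP, which is not at hand. The word nominal may mean only the level before adjustment, and a 5% threshold could be applied to adjusted p-values without contradicting the sentence. Section 3 labels microbiota and metabolomics exploratory, and Section 10 calls the trial proof-of-concept.

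Much of this stands. It lowers the weight of the point, and the protocol does not forbid a correction in the SAP. It does not remove the point, because the protocol makes a positive statement about all tests. The SAP reference closes the biomarker sentence and does not qualify either the 5% sentence or the microbiota sentence. An exploratory label does not make 5% per taxon a sound criterion for calling a taxon significant.

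A reader might also draw stronger conclusions that the document does not support:

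- That tens of false findings follow from the plan. They follow only from an assumed feature count.
- That every metabolite will be tested one by one. Section 12 names no metabolite test.
- That at least one false secondary finding is 92% likely. That figure needs independence. The tests share a placebo arm, repeat the same markers at 3 and 6 weeks, and overlap (the 5–24 h urine lies within the 0–24 h collection).
- That the open wording of the biomarker list lets hits be chosen afterwards. The SAP may fix the list. Whether to close it, or to correct the secondary tests formally, is a trade-off and not an error in the protocol.

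**Conclusion.** The point holds as a limited, inexpensive improvement. As written, Section 12 would let individual taxa and functional features be called significant at an unadjusted 5%. The size depends on a number that the protocol does not give: about 10 to 60 false hits for 50 to 300 taxa over two contrasts and two timepoints, or 5 for 50 taxa at one timepoint, if neither product works. The 50 countable secondary tests add 2.5 expected false positives. That number is small enough to be dealt with by open labelling. The conclusion on the primary endpoint is not affected.

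**What to change.** Amend the 5% sentence in Section 12 so that it does not cover high-dimensional feature-by-feature testing: taxa, functional features, and metabolites if they are tested one by one. State that such a feature is called significant only after Benjamini-Hochberg false discovery rate control at a pre-stated level, for example 5% or 10%. Apply it within each data block (genus, species, functional features, and faecal and blood metabolites where applicable) and each product-versus-placebo contrast. Say whether the two timepoints belong to the same family. Add that secondary endpoint p-values are reported as nominal and unadjusted.

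This takes a sentence or two in Section 12 and a matching entry in the SAP, with no change to visits, samples or sample size. The downside is a shorter list of significant features. In the family of 200 tests used above, the smallest p-value would have to reach 0.05/200 = 0.00025 to be called on its own at a 5% rate, or 0.10/200 = 0.0005 at 10%. With 25 randomised per arm, weaker true effects may then go uncalled. They can still be shown with estimates and unadjusted p-values, labelled as such.
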